#### Recruitment and consent

Potential participants will be identified through their previous participation in work package 1. Patients scored as “pre-frail” will randomly be selected to participate in work package 2. Patient information sheets will be given to the patients in advance of a discussion with the researcher either by post or in person. Individuals will be approached at their usual dialysis unit appointment for discussion and potential recruitment to the study. Potential participants will be given the opportunity to reflect on the information given both verbally and within the written information sheet. No fixed time is specified for the length or timing of this prior interview as it will be dependent upon the patient’s understanding of their underlying disease and of the research project. A certain level of English proficiency will be necessary to participate in the intervention, however it is important that non-native English speaking patients are given full opportunity to participate in this study and the same methods will be used as in work package 1 to facilitate this. Written consent will be received from each patient entering the study. A study patient identifier will be allocated and recorded on the study recruitment log.

Work package 1 patients who meet eligibility criteria will be randomly selected for participation in work package 2 using REDCap™ (in random permuted blocks within strata to balance numbers and characteristics). Participants who have subsequently been approached and given consent to participate in work package 2 will be randomised once more using REDCap™ (in random permuted blocks within strata to balance numbers and characteristics) into one of the following lifestyle intervention groups (*n* = 25 for each intervention group for a total of 50 participants). As part of the cm-RCT design, data from pre-frail work package 1 patients who were eligible but not selected for participation in work package 2 will provide a further comparator group for analysis. As an open-label study, neither participants nor researchers will be blinded to group allocation.

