#### Passive control group

This group will receive their usual standard of care from their treating dialysis centre, including usual dietitian input. However, there will be no psychosocial intervention or focused exercise and dietary monitoring programme. Follow-up will be at routine clinic visits only, where lifestyle modification advice will be reinforced as per usual clinical practise. Physiotherapy may be offered to these patients as per standard referral guidelines but will not have the psychosocial underpinning of the intervention group.

Both groups will undergo a repeat frailty testing during the mid-point (3 months ± 2 weeks) and the end of study intervention (6 months ± 2 weeks) (see Figs. 1 and 2). The aim is to assess if there is any change in frailty status which will provide data to underpin a power calculation for a subsequent large-scale study. Additional pre-specified secondary outcomes will be collected as highlighted below in the protocol. Participants will also be invited to complete a series of questionnaires to ascertain the tolerability and suitability of the intervention trial, and to guide the delivery of the trial on a larger scale.

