### Study outcomes

#### Primary endpoint

The primary endpoint is the feasibility and tolerability of the clinical intervention study (recruitment rates, loss to follow-up, and study withdrawal).

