#### Secondary endpoints

Secondary endpoints include: 1) refinement of the multi-disciplinary intervention based upon views from participants and stakeholders (from post-study questionnaires); 2) change in frailty status (based on Fried Frailty Phenotype, Clinical Frailty Scale); 3) difference in clinical and biochemical outcomes; 4) quality of life score (EQ-5D-3 L); 5) receipt of kidney transplant; 6) vascular access failure; and 7) long-term clinical outcomes (death, cardiac events, hospitalisation) to University Hospital Birmingham electronic patient records and Hospital Episode Statistics

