#### Statistics

The principle parameters being examined in work package 1 are hospitalisation, mortality, and their association with frailty. Based upon US data [6], we have assumed an adjusted risk ratio of 2.24 for 1-year mortality and 1.56 for 1-year mortality and/or hospitalisation for frail versus non-frail patients receiving haemodialysis. We have assumed a baseline (non-frail) risk of 5% for 1-year mortality and a 40% risk of 1-year mortality/hospitalisation, powered to 0.8 and with a confidence interval of 0.95. We therefore calculate a sample size of 602 to be adequately powered to demonstrate a difference in 1-year mortality or 150 patients to be powered for 1-year mortality/hospitalisation.

Work package 2 is designed as a feasibility study so no specific power calculations have been made. However, one of the secondary outcomes is to use the data regarding effect sizes to determine the sample required for a larger multi-centre study based upon the feasibility of work package 2.

Statistical analysis will be performed using standard software (SPSS Version 25, Mac version, Chicago, USA). Normality of data will be assessed using the Kolmogorov-Smirnov tests. Paired sample *t* test and Wilcoxon signed rank test, for parametric and non-parametric data respectively, will be used to compare the means of two variables from a single group. Comparison of data between groups will be made using unpaired student *t* tests and the Mann-Whitney test for parametric and non-parametric data, respectively. Categorical data will be analysed using Pearson’s or Spearman’s test as appropriate. A *p* value < 0.05 is considered significant in the statistical analysis.

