Work package 2 is an unblinded, randomised controlled study using a psychologically supported multi-disciplinary intervention into frailty compared with a control group which receives standard care. This will be used as a basis for exploring whether a large scale, multi-centre trial is feasible and warranted, while also providing data upon effect sizes to allow subsequent power calculation for such a study. We chose the “pre-frail” group as the focus of this intervention, firstly because they arguably have the most to gain—not progressing to frailty—and, secondly, because pre-frailty represents a much less heterogeneous group than frailty, the latter of which would include essentially functionally independent individuals with a few accumulated deficits along with bed-bound individuals and those approaching end-of-life. The pre-frail group therefore have an easily definable set of characteristics and have the ability to participate in, and benefit from, the proposed interventions.

One of the principle strengths of the study design is the breadth of data being collected. Researchers will collect data on multiple aspects of frailty from consenting patients to include aspects of sarcopenia (muscle mass, quality, and function), immunosenescence, functional status/disability, mood, cognitive status, and medical history. This rich dataset will allow detailed analysis of the heterogeneity or otherwise of frailty within the cohort. As work package 1 is a single time-point analysis with electronic follow-up thereafter, dropout should be minimal and large numbers of patients could be recruited to allow such detailed analysis to have real meaning to clinicians. Another strength lies in the cm-RCT design, whereby stratified random sampling will identify trial participants from consenting eligible cohort study participants. This approach has several benefits, including amelioration of potential attrition bias in the control group, long-term data follow-up for a large comparator group, and increased power for the study [34].

A weakness of the study is the single time-point assessment in work package 1, as frailty is known to change over time [45–47]. Nevertheless, objective frailty measurements still hold prognostic value [48].

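### The blanket p < 0.05 rule in Statistics is not limited to work package 1, so it also covers the unpowered 25 v 25 comparisons of work package 2

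*Protocol article*

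**What the plan says.** The Statistics section covers both work packages. It sizes work package 1, then says: "Work package 2 is designed as a feasibility study so no specific power calculations have been made". A general paragraph follows that names paired tests, unpaired between-group tests and tests for categorical data, and closes with the rule that a p "value < 0.05 is considered significant in the statistical analysis". Nothing restricts that paragraph to work package 1.

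The paragraph does reach work package 2. Methods/design says that work package 2 will compare active intervention with standard care on frailty and outcomes. Recruitment and consent gives the size: "25 for each intervention group for a total of 50 participants". Passive control group adds: "Both groups will undergo a repeat frailty testing during the mid-point (3 months ± 2 weeks) and the end of study intervention (6 months ± 2 weeks". Secondary endpoints include "change in frailty status (based on Fried Frailty Phenotype, Clinical Frailty Scale"), EQ-5D, transplant, vascular access failure, death, cardiac events, hospitalisation, and an unspecified set of clinical and biochemical outcomes.

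The primary endpoint is separate and is not an efficacy test: "The primary endpoint is the feasibility and tolerability of the clinical intervention study (recruitment rates, loss to follow-up, and study withdrawal"). Passive control group, Statistics and Discussion all give the use of the frailty data as informing the sample size of a later study. Discussion adds that work package 2 is a basis for "exploring whether a large scale, multi-centre trial is feasible and warranted".

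**The concern.** A feasibility trial that declares no power has no planned basis for calling a between-arm difference significant or not significant. As written, the rule permits both for any work package 2 comparison. Two things follow.

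- Several unadjusted tests give a noticeable chance of a nominally significant result when nothing is going on.
- The trial is small, so a real but moderate effect will usually miss the threshold. When it does pass, the estimate will tend to be too large.

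The second matters more here, because the effect estimates are to feed a sample-size calculation. If an outcome were carried forward because it was significant, the next trial would tend to be too small. Conversely, a non-significant frailty result could be misread as showing no effect.

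**Working it through.** **1. The plan's own figures, to fix the meaning of 0.05.** The article does not state whether its tests are one- or two-sided. Work package 1 is "powered to 0.8 and with a confidence interval of 0.95". Use the unpooled two-proportion formula with equal groups, n per group = (1.960 + 0.842)² × [p1(1 − p1) + p2(1 − p2)] / (p2 − p1)², where (1.960 + 0.842)² ≈ 7.85.

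- Mortality: p1 = 0.05, p2 = 0.05 × 2.24 = 0.112. n = 7.85 × 0.14696 / 0.003844 ≈ 300.1, rounded up to 301, total 602.
- Mortality/hospitalisation: p1 = 0.40, p2 = 0.40 × 1.56 = 0.624. n = 7.85 × 0.47462 / 0.050176 ≈ 74.2, rounded up to 75, total 150.

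Both published totals reproduce with two-sided 0.05, which is used below. The article gives no corresponding figure for work package 2.

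**2. Number of comparisons.** Two frailty scales × two times = 4. EQ-5D, transplant, access failure, death, cardiac events and hospitalisation add 6, which makes 10. This leaves out the questionnaire-based endpoint, which is not naturally a between-arm test, and the unspecified clinical and biochemical outcomes, which would add tests.

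**3. Chance of at least one p < 0.05 with no true effect.** If the tests are independent, it is 1 − 0.95¹⁰ = 40.1%. For correlated tests, equicorrelated normal statistics were simulated. The correlations are assumptions, since the article gives none.

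| Assumed correlation | Either direction | Favouring active arm |
|---|---|---|
| 0 | 40% | 22% |
| 0.3 | 35% | 18% |
| 0.5 | 29% | 14% |
| 0.7 | 21% | 11% |

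The four frailty tests alone give 13% to 19% in either direction.

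**4. Sparse events.** At an assumed 5% event rate per arm (the article's non-frail 1-year mortality), Pearson's test at 25 v 25 rejects only about 2% of the time. If four of the event endpoints behave like this, the figures at correlation 0.5 fall to about 23% in either direction and 12% favouring the active arm. At an 11% event rate the test is close to 5% and the reduction disappears.

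**5. Power and threshold at 25 per arm.** The standard error of a standardised difference is √(2/25) = 0.283. The two-sided critical t on 48 degrees of freedom is 2.011, so an observed difference must exceed 2.011 × 0.283 = 0.57 SD to be significant. Power (t test) is 18% for a true effect of 0.3 SD, 41% for 0.5 SD and 79% for 0.8 SD. These figures assume that all 50 participants contribute data.

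**6. Overstatement.** Suppose the true effect is 0.5 SD. By the normal approximation (threshold 1.96 × 0.283 = 0.55 SD), estimates that reach significance in the favourable direction average about 0.76 SD. Sample size varies with 1/effect², so planning on 0.76 instead of 0.5 gives a trial too small by a factor of (0.76/0.5)² ≈ 2.3.

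**The case against.** The strongest reply is that the threshold is a conventional closing sentence in a general paragraph that assigns no test to any work package 2 endpoint. The feasibility framing is already explicit: the primary endpoint is feasibility, the lack of power is disclosed, and the frailty data are for planning. Unadjusted secondary endpoints in a feasibility study are not an error in themselves. An exploratory label, an order among the secondary endpoints and a lead frailty scale or time point are details that a full protocol or analysis plan commonly supplies, and neither is shown. All of this stands, and the absence of those details is no finding here. What it does not answer is that the published rule is unrestricted as it stands and applies significance calls to comparisons that the same section leaves unpowered.

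A reader might infer more than the article supports:

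- That every secondary endpoint will be declared significant or not. The first concerns refining the intervention from questionnaires.
- That the endpoints have no hierarchy. The feasibility primary endpoint is clearly separated from the secondary ones.
- That a chance positive is likely. On the named comparisons it stays below one half, and is about 11% to 22% in the direction that would favour the intervention.
- That a significant secondary result would settle whether a large trial is warranted. No progression rule uses a p value, so that route is conjecture.

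**Conclusion.** The point holds as a minor one. A single significance rule, fixed for the whole analysis, extends to an unpowered 25 v 25 feasibility comparison whose stated purpose is effect estimation. The size of the problem is a 21% to 40% chance of at least one nominal positive, 41% power at 0.5 SD, and a threshold of about 0.57 SD that filters for overestimates. The first range rests on a count of ten tests and assumed correlations of 0 to 0.7. Sparse events would lower it and the unspecified clinical and biochemical outcomes would raise it. The factor of 2.3 in planning the next trial applies only if the true effect is 0.5 SD and an outcome is chosen because it was significant, which the article does not say will happen.

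**What to change.** In Statistics, limit the p < 0.05 rule to work package 1. Add that the active v passive secondary comparisons in work package 2 are exploratory and will be reported as estimates with 95% confidence intervals, without significance statements. State that progression to a larger trial rests on the primary feasibility results (recruitment, loss to follow-up, withdrawal), and that the frailty effect estimates, with their intervals, are used only for sizing. No multiplicity adjustment is needed.

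The cost is a few sentences, with no new data or participants. The one thing given up is being able to call a pilot secondary result significant.

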## Discussion

Frailty has been linked with adverse outcomes in North American haemodialysis cohorts [5–12, 17, 39, 40], but these data are not transferrable to UK patients since US dialysis populations have adverse outcomes compared with UK populations [18]. There is no agreement over the best frailty tool to assess patients, both within the general population and within haemodialysis cohorts. The Fried Frailty Phenotype [41] and Rockwood Frailty Index [42] are the most commonly cited instruments in geriatric and renal-specific literature, with the Clinical Frailty Scale also featuring in haemodialysis cohorts [12]. The Edmonton Frail Scale is recommended by the British Geriatric Society, but has yet to be validated in patients receiving haemodialysis [43]. We expect each of these instruments to show association with negative outcomes, but it is not yet known which of these provides the best predictive value in patients receiving haemodialysis. The cohort analysis embedded within this study will therefore seek to address this by comparing frailty instruments for their association with negative outcomes, whilst also addressing renal-specific outcomes such as transplantation or dialysis access failure. These data will allow renal practitioners to better understand which frailty tool is optimal for their population.

Multi-disciplinary intervention into frailty has shown promise [19], although a systematic review and meta-analysis was limited by the lack of validated measures of frailty as inclusion criteria and outcome measures in the published studies to date [22]. To our knowledge, there are no published data regarding frailty interventions within the UK haemodialysis population, although a US study showed self-reported disability could be reduced by such an intervention [20].

There is an urgent need for the development of interventions capable of enacting long-term change within patient groups. Our experience in Birmingham suggests that BCTs can modify behaviour with the potential to change clinical outcomes [33, 44]. Therefore, a patient-centred, frailty-specific BCT intervention may be beneficial for frail patients receiving haemodialysis and may improve clinical and patient-reported outcomes.

Work package 2 is an unblinded, randomised controlled study using a psychologically supported multi-disciplinary intervention into frailty compared with a control group which receives standard care. This will be used as a basis for exploring whether a large scale, multi-centre trial is feasible and warranted, while also providing data upon effect sizes to allow subsequent power calculation for such a study. We chose the “pre-frail” group as the focus of this intervention, firstly because they arguably have the most to gain—not progressing to frailty—and, secondly, because pre-frailty represents a much less heterogeneous group than frailty, the latter of which would include essentially functionally independent individuals with a few accumulated deficits along with bed-bound individuals and those approaching end-of-life. The pre-frail group therefore have an easily definable set of characteristics and have the ability to participate in, and benefit from, the proposed interventions.

One of the principle strengths of the study design is the breadth of data being collected. Researchers will collect data on multiple aspects of frailty from consenting patients to include aspects of sarcopenia (muscle mass, quality, and function), immunosenescence, functional status/disability, mood, cognitive status, and medical history. This rich dataset will allow detailed analysis of the heterogeneity or otherwise of frailty within the cohort. As work package 1 is a single time-point analysis with electronic follow-up thereafter, dropout should be minimal and large numbers of patients could be recruited to allow such detailed analysis to have real meaning to clinicians. Another strength lies in the cm-RCT design, whereby stratified random sampling will identify trial participants from consenting eligible cohort study participants. This approach has several benefits, including amelioration of potential attrition bias in the control group, long-term data follow-up for a large comparator group, and increased power for the study [34].

A weakness of the study is the single time-point assessment in work package 1, as frailty is known to change over time [45–47]. Nevertheless, objective frailty measurements still hold prognostic value [48].

This cohort randomised controlled trial will assess the prevalence and associations of frailty using validated measurement tools and test the utility of these instruments in predicting adverse outcomes. The study will also assess the feasibility of conducting a randomised controlled trial using an intervention designed to improve frailty.

## Abbreviations

AE: Adverse event
BAME: Black, Asian and minority ethnic
BCT: Behavioural change technique
CBT: Cognitive behavioural therapy
cm-RCT: Cohort multiple randomised controlled trial
EPR: Electronic patient record
MoCA: Montreal Cognitive Assessment
NHS: National Health Service
NLM: Node-link mapping
PHQ: Patient Health Questionnaire
PIL: Patient information leaflet
REC: Research Ethics Committee
REDCap: Research Electronic Data Capture
SAE: Serious adverse event
SBNT: Social behaviour and network therapy
